# Biomarker-based assessment of cerebral small vessel disease progression after ischemic stroke – a prospective cohort study (MA-BIO)

**DOI:** 10.1186/s42466-026-00514-3

**Published:** 2026-08-17

**Keywords:** Stroke, Cerebral small vessel disease, Biomarkers, Magnetic resonance imaging, Cognitive assessment

## Abstract

**Background:**

Cerebral small vessel disease (CSVD) is a leading cause of ischemic stroke and vascular cognitive impairment, yet currently lacks clinically established biomarkers for monitoring disease activity. While clinical routine magnetic resonance imaging (MRI) can provide quantitative measures of structural brain changes, it does not capture ongoing pathophysiological processes. Blood-based biomarkers offer a minimally invasive approach to detect dynamic changes in CSVD and may provide novel insights into mechanisms of progression and potential targets for intervention. This study aims to evaluate longitudinal trajectories of candidate blood biomarkers and their association with MRI-derived markers and cognitive outcomes in patients with CSVD.

**Methods:**

In this single-center, prospective observational cohort study at the University Hospital Ulm, Germany, up to 180 adults with MRI-proven evidence of CSVD will be recruited and stratified into three groups: (1) CSVD without acute ischemic stroke, (2) CSVD with acute lacunar ischemic stroke, and (3) CSVD with territorial ischemic stroke. Participants will undergo comprehensive assessments at baseline, at 3, 6, and 12 months after enrollment. The primary outcome is defined as longitudinal changes of White Matter Hyperintensities (WMH) volumes. Secondary outcomes upon one year include DTI-derived measures, changes in blood biomarkers, cognitive performance, clinical functional measures, and incidence of new cerebrovascular events. Imaging, neurovascular ultrasound, and neuropsychological assessments will be conducted using standardized protocols. Clinical primary and secondary outcomes will be correlated to post-mortem CSVD pathology in the brain in prospectively studied patients, who have consented to autopsy.

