Beyond brain MRI, no clinically established in vivo surrogate marker for CSVD activity currently exists. Blood-based biomarkers represent a promising approach for monitoring longitudinal disease activity and potential regression. Of those, serum neurofilament light chain (NfL) levels seem in particular promising as they have been found to reflect imaging burden and neuropsychological features (processing speed performance) of CSVD in a cross-sectional study including more than 500 patients [14]. Furthermore, temporal changes of serum NfL have been described in a monocenter cohort of 79 patients after a recent small subcortical infarct upon 15 months. Compared to healthy controls, NfL levels were increased shortly after stroke and until 3 months, returning to normal levels after 15 months [15]. New incident ischemic lesions on MRI were reflected by secondary NfL increases [15]. Further results from the Alzheimer’s Disease Neuroimaging Initiative (ADNI) showed that plasma NfL correlated positively with CSVD severity, and with the presence of cerebral microbleeds (CMBs) and lacunes [16]. With higher the changes in plasma-NfL were over time, the CSVD burden and WMH increased upon a mean follow-up of 27 months in 378 patients [16]. These findings imply an additional value of blood NfL measurements for disease monitoring, which may be complementary to brain MRI.

In a monocenter, prospective registry, serum GFAP correlated with verbal fluency, visuomotor and executive functions in patients with CSVD [17]. Lately, in a follow-up study over 12 months, vascular endothelial growth factor (VEGF) levels in the blood were associated with incident brain lesions in a longitudinal study [18]. Beyond that, such biomarkers have demonstrated substantial diagnostic and longitudinal value in other neurological disorders, including multiple sclerosis and neurodegenerative diseases [19, 20].

The present prospective cohort study builds upon a previously conducted single-center pilot study by our group (local Ethics approval no. 343/22), which demonstrated the feasibility of longitudinal biomarker measurements in patients with CSVD and provided preliminary evidence supporting associations between biomarker dynamics and MRI-detected CSVD progression.

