The objectives of the presented study include the identification of one blood biomarker or a set of biomarkers that can help identify disease progression in CSVD. A further aim is to describe differences of biomarker courses in direct comparison of patients with CSVD and acute lacunar ischemia with patients with territorial ischemia in a prospective, consecutive and multi-modal trial.

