### Eligibility criteria

Patients are eligible as participants if (a) their age is ≥ 18 years and if (b) brain MRI provides evidence of CSVD, defined as WMH (Fazekas grade 1–3). Patients with Fazekas grade 1 will be included as well to cover all different stages of CSVD and because even a mild lesion load has been linked to neurocognitive impairment [21]. In case of uncertainty about the aetiology of WMH, diagnostics to rule out inflammatory diseases or genetic small vessel diseases are planned. Furthermore, (c) patients must be assigned to one of the following groups based on MRI findings: Group 1: CSVD without evidence of an acute ischemic stroke, Group 2: CSVD with acute lacunar ischemic stroke, defined as singular diffusion-weighted imaging (DWI)-hyperintense, apparent diffusion coefficient (ADC)-hypointense lesion on brain MRI with a diameter of maximum of 2.5 cm, or group 3: CSVD with acute territorial ischemic stroke pattern on MRI. All patients must be (d) able to provide written informed consent and (e) have sufficient German language skills to understand study procedures and assessments. The requirement for sufficient German language skills is necessary to ensure valid neuropsychological assessments. However, this criterion may introduce selection bias and may limit the generalizability of the study findings.

Inclusion criteria are as follows:

Age ≥ 18 years.Evidence of CSVD on brain MRI, defined as the presence of WMH (Fazekas grade 1–3).Assignment to one of the defined study groups based on MRI findings.Ability to provide written informed consent.Sufficient German language skills.

Exclusion criteria are as follows:

Alternative plausible causes of WMH other than CSVD.Known neurodegenerative diseases.Acute or recent traumatic brain injury.Contraindications to MRI.Pregnancy or breastfeeding.Expected life expectancy of less than one year.Inability to comply with study procedures or follow-up visits.Severe renal insufficiency with an estimated glomerular filtration rate <15 ml/min

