### Recruitment

The recruitment is carried out by a designated study team of the Department of Neurology, University Hospital Ulm, Germany, during the in-patient stay of patients eligible for participation in Groups 2 and 3. Patients with CSVD without a current stroke are recruited at our specialized outpatient clinic for CSVD and cerebrovascular diseases. As of June 11th, 2026 6 male patients and 3 female patient were enrolled. Of those, 5 (56%) presented with acute territorial stroke and were recruited in Group 3, 3 had a lacunar stroke and were assigned to group 2 (33%) and one further participant without acute stroke was recruited into group 1 (11%). The median age was 68 years with a minimum of 52 and a maximum of 85 years.

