### Biosamples

At all scheduled study visits, venous blood samples will be collected, processed, aliquoted, and stored in the biobank of the Department of Neurology according to established standard operating procedures. Laboratory analyses include a comprehensive panel of vascular, metabolic, inflammatory, and neurodegeneration-related parameters. Vascular and metabolic markers comprise lipid parameters (Low- and high-Density Lipoprotein (LDL, HDL), cholesterol, triglycerides, and lipoprotein(a)) as well as markers of glucose metabolism, including insulin and glycated hemoglobin (HbA1c). Cardiac biomarkers (troponin I or T) at baseline in groups 2 and 3 and inflammatory markers, including high-sensitivity C-reactive protein, interleukin-6, and interleukin-1 alpha, are assessed to characterize systemic vascular and inflammatory status [27].In addition, blood-based biomarkers reflecting central nervous system injury are analyzed, e.g. GFAP as a marker of glial activation, neurofilament light chain (NfL) as a marker of axonal damage, phosphorylated tau 217 (pTau217) as an exploratory neurodegeneration-related biomarker, and beta-synuclein as an exploratory synaptic marker.

CSF samples obtained as part of routine clinical care and based on clinical indication (e.g. to exclude inflammation or vasculitis) will be used for biomarker analyses, including total tau protein, phosphorylated tau, and amyloid-β1–42. In addition, endothelial cell–related biomarkers, including endothelin-1 and vascular cell adhesion molecule-1 (VCAM-1), are analyzed to capture endothelial dysfunction associated with cerebral small vessel disease [28, 29].

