### Plans to promote participant retention and complete follow-up

In order to enhance participant retention, follow-up visits are coordinated to reduce burden and optimize adherence. The scheduled MRIs are performed in conjunction with study visits, accordingly, we can avoid additional appointments for the sole purpose of MRI. MRI is performed on a scanner next to the outpatient department. Participants receive direct DECT telephone contact numbers and email addresses of the study team members.

A complete and condensed overview of the study visits and procedures is given in Table 2.

**Table 2 Tab2:** Study assessments alongside the visits 1-4

Schedule of assessments				
Visits	1	2	3	4
	Screening and baseline	Follow-up	Follow-up	End-of-study
Months after enrollment	0	3	6	12
Assessment				
Informed Consent	x			
Medical History	x	x	x	x
NIHSS	x	x	x	x
mRS	x	x	x	x
MRI	x		x	x
Basic NPA	x	x	x	x
Extended NPA	x			x
NVDU	x	x	x	x
Biomarkers	x	x	x	x
Blood Laboratory	x	x	x	x

NIHSS, National Institutes of Health Stroke Scale, mRS, modified Rankin Scale; MRI, Magnetic Resonance Imaging; EQ-5D, EuroQol 5 Dimension; extended NPA, Neuropsychologic Assessment; NVDU, neurovascular Doppler ultrasound; biomarkers: refers to blood-based biomarkers

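### Visits are timed from enrolment, not stroke onset, so days since stroke at the baseline sample are only loosely bounded and could differ between the lacunar and territorial groups

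*Protocol article*

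**What the plan says.** **Clock.** The Abstract (Methods) states: "Participants will undergo comprehensive assessments at baseline, at 3, 6, and 12 months after enrollment". Tables 1 and 2 use the same clock, with the row label "Months after enrollment" and a single schedule for all three groups.

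**Sampling.** Under Biosamples: "At all scheduled study visits, venous blood samples will be collected, processed, aliquoted, and stored in the biobank". The baseline biomarker value is therefore the value at the enrolment visit.

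**Limits on time since stroke.** Under Eligibility criteria, Group 2 is "defined as singular diffusion-weighted imaging (DWI)-hyperintense, apparent diffusion coefficient (ADC)-hypointense lesion on brain MRI with a diameter of maximum of 2.5 cm" and the third group is "group 3: CSVD with acute territorial ischemic stroke pattern on MRI". Neither definition gives hours or days from onset. Under Recruitment, enrolment takes place "during the in-patient stay of patients eligible for participation in Groups 2 and 3". The length of that stay is not stated.

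**Comparison affected.** The Introduction gives as a further aim to "describe differences of biomarker courses in direct comparison of patients with CSVD and acute lacunar ischemia with patients with territorial ischemia".

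**Evidence on timing.** The Introduction cites a cohort of 79 patients with a recent small subcortical infarct, in whom "NfL levels were increased shortly after stroke and until 3 months, returning to normal levels after 15 months".

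**Analysis.** Statistical methods plans individual slopes from mixed models with random intercepts, then a comparison of slopes between groups. Time since onset is named neither as the time axis nor as a covariate.

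**The concern.** In a comparison of courses after stroke, the natural origin is the stroke. Enrolment comes later by an amount that depends on when the patient is approached and can consent. Two patients with the same true marker course, one sampled on day 1 and the other on day 10, both supply a month-0 value but from different points on the curve.

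If delays scatter equally in both groups, the result is extra variance in the most time-sensitive sample. If the mean delay differs between groups, part of any difference in baseline level or in change from baseline reflects the day of sampling and not the type of stroke. The bias could run in either direction, so it could create a difference or hide one. Labelling results as hypothesis-generating does not remove it, because the hypothesis generated could be a timing artefact.

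**Working it through.** **Step 1. Does the article align patients by onset?**
- The clock is enrolment wherever the schedule is stated (Abstract, Table 1, Table 2).
- Two conditions bound the onset-to-enrolment time: an acute stroke on MRI and recruitment during the in-patient stay. Both apply to both stroke groups.
- The in-patient rule is the same for everyone, but the window it creates lasts as long as each patient's stay. It bounds the delay without equalising it.

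So patients are not aligned by onset, although the delay is not unlimited.

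**Step 2. Does time since onset matter for the markers?** On the article's own account NfL is raised soon after stroke and up to 3 months, and normal by 15 months. No rate of change per day is given, and the evidence concerns small subcortical infarcts only.

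**Step 3. The plan's own sensitivity figures, as a scale.** Sample size states detectable between-group differences of d ≈ 0.51 (60 per group) and 0.59 (45 per group), for WMH change. With d = (z0.975 + z0.80) × √(2/n):
- n = 60: (1.960 + 0.842) × √(2/60) = 0.511
- n = 60 × (1 − 0.25) = 45: (1.960 + 0.842) × √(2/45) = 0.591

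Both reproduce. They say nothing about timing, but they show what a shift of a given number of SDs means at these group sizes.

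**Step 4. Illustration of a timing shift.** The documents give neither a delay by group nor a marker change per day, so both are assumed here: a change of 0.1 to 0.5 SD per week in the early period, and a difference in mean delay of 0, 2 or 7 days. There is no true group difference.

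Shift b = (SD per week) × (days ÷ 7). The chance that a two-sided 5% t-test declares a group difference comes from the noncentral t distribution with 2n − 2 degrees of freedom and noncentrality b × √(n/2).

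| Difference in mean delay | Assumed change per week | Shift b | Rejection, 45 per group | Rejection, 60 per group |
|---|---|---|---|---|
| 0 days | any | 0 | 5.0% | 5.0% |
| 2 days | 0.1 SD | 0.03 SD | 5.2% | 5.3% |
| 2 days | 0.5 SD | 0.14 SD | 10.3% | 12.1% |
| 7 days | 0.1 SD | 0.10 SD | 7.6% | 8.4% |
| 7 days | 0.25 SD | 0.25 SD | 21.6% | 27.4% |
| 7 days | 0.5 SD | 0.50 SD | 65.0% | 77.5% |

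**Step 5. Where the effect falls.** Seven days is 7/91 = 7.7% of the interval to the 3-month visit and 7/365 = 1.9% of that to the 12-month visit. Any artefact therefore lies mainly in the baseline sample and in whatever is measured relative to it.

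**The case against.** **Same rule for both groups.** Both stroke groups need an acute stroke on MRI and are recruited in hospital. No section gives the delay in either group or says that the delays differ. This stands: a difference between groups is a risk, not an established fact.

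**Territorial patients enrolled later.** A reader might infer this from the remark on mobility and morbidity under Sample size. The documents do not support it: that remark explains drop-out from follow-up visits and says nothing about later consent, later enrolment or longer stay.

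**Looser acuity criterion for Group 3.** A reader might infer this because only Group 2 has an ADC condition. The asymmetry is weak. Group 3 must also be acute on MRI, and Postprocessing describes the DWI/ADC core of the acute stroke, and the handling of acute DWI lesions on the baseline scan, without separating groups. Much of the extra Group 2 wording serves to define a lacunar lesion.

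**Condensed article, unseen SAP.** A sampling window, date fields or a timing covariate may exist elsewhere. This is fair, and the point therefore rests on what the article does fix, namely enrolment as the clock. If the full documents already use onset dates, one clarifying sentence settles it.

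**Low stakes.** The primary outcome is WMH volume change, and no effect on it is shown. The comparison concerned is a further, descriptive aim without confirmatory claims. This limits the weight of the point, but the comparison is still a stated objective.

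**Conclusion.** The point holds as a risk. The stated clock does not align Groups 2 and 3 by stroke onset, the time from onset to the baseline sample is only loosely bounded, and the article's own evidence makes time since stroke relevant to NfL. The comparison of biomarker courses is exposed to added noise and to possible confounding, chiefly at baseline and in change from baseline.

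The size cannot be derived from the documents. It is zero if mean delays are equal and grows with any difference. Under the assumed 0.1 to 0.5 SD per week, the shift is 0.03 to 0.14 SD for a 2-day difference and 0.10 to 0.50 SD for a 7-day difference.

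A reader might go further and infer that the two groups' courses do start at different times after stroke, or quote a definite fold-difference at baseline. Neither is supported: such a figure needs an assumed lag and an assumed daily change, and at zero lag the ratio is 1.

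**What to change.** 1. For Groups 2 and 3, record the date of stroke onset (last known well) and the date of each blood sample.
2. Report the interval from onset to baseline sample by group.
3. In the Group 2 versus Group 3 biomarker comparison, use days since onset as the time variable in place of months since enrolment, or adjust for the onset-to-sample interval. The time term should allow curvature: in a straight-line model, moving each patient's origin changes mainly the intercept and leaves the slope nearly unchanged.
4. Group 1 has no index stroke and keeps enrolment as time zero.

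The cost is two date fields and somewhat more analysis work, with no change to eligibility or visit schedule. Of the 9 patients enrolled by 11 June 2026, 5 + 3 = 8 were in the stroke groups. Their dates should be recoverable, since they were recruited as in-patients.

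A fixed window from onset to baseline sample is not needed for this. It could exclude territorial patients who consent late, and would still leave differences in timing within the window.

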**Discussion:**

By integrating blood-based biomarkers with advanced imaging and longitudinal cognitive assessments, this study aims to advance our understanding of CSVD pathophysiology and may identify biomarkers of disease activity. Our findings hopefully inform future precision-medicine approaches and novel therapeutic strategies.

**Trial registration:**

German Clinical Trials Registry (DRKS00038936), registered February 3, 2026.

## Introduction

Cerebral small vessel disease (CSVD) is a major cause of ischemic stroke and contributes substantially to vascular cognitive impairment and subsequent dementia, accounting for approximately one quarter of ischemic strokes and vascular dementias [1]. Key neuroimaging correlates of CSVD include white matter hyperintensities (WMH), cerebral microbleeds, lacunes, perivascular spaces, and superficial siderosis, which can be assessed by brain magnetic resonance imaging (MRI) [1, 2]. Hence, brain MRI is considered the diagnostic reference standard and also allows quantitative assessment of CSVD burden, including volumetric evaluations [2, 3]. Advanced MRI techniques such as diffusion tensor imaging (DTI), amongst other techniques, can enable further characterization of microstructural white matter injury beyond conventional WMH assessment [4, 5].

Recent neuroimaging studies indicated that CSVD may show mild partial regression in an observation over several years, highlighting the dynamic nature of the disease [6, 7]. From a therapeutic perspective, evidence supports antihypertensive treatment as a secondary preventive strategy [1, 4]. In addition, randomized clinical trials suggest that pharmacological approaches such as the combination of cilostazol and isosorbide mononitrate may reduce stroke recurrence and improve functional and cognitive outcomes, although the generalizability of these findings is uncertain [8]. Longitudinal observational studies suggest that WMH progression may be accelerated following lacunar stroke compared with asymptomatic individuals, particularly in patients with higher baseline CSVD burden [9, 10]. With higher degrees of dysconnectivity as a result of acute stroke and preexisting CSVD affecting deep WM, functional outcome is worse [11]. However, available data are based on datasets of observational and interventional prospective trials on CSVD or ischemic stroke and do not adequately clarify how stroke mechanism, size, and localization impact on CSVD progression [12, 13].

Beyond brain MRI, no clinically established in vivo surrogate marker for CSVD activity currently exists. Blood-based biomarkers represent a promising approach for monitoring longitudinal disease activity and potential regression. Of those, serum neurofilament light chain (NfL) levels seem in particular promising as they have been found to reflect imaging burden and neuropsychological features (processing speed performance) of CSVD in a cross-sectional study including more than 500 patients [14]. Furthermore, temporal changes of serum NfL have been described in a monocenter cohort of 79 patients after a recent small subcortical infarct upon 15 months. Compared to healthy controls, NfL levels were increased shortly after stroke and until 3 months, returning to normal levels after 15 months [15]. New incident ischemic lesions on MRI were reflected by secondary NfL increases [15]. Further results from the Alzheimer’s Disease Neuroimaging Initiative (ADNI) showed that plasma NfL correlated positively with CSVD severity, and with the presence of cerebral microbleeds (CMBs) and lacunes [16]. With higher the changes in plasma-NfL were over time, the CSVD burden and WMH increased upon a mean follow-up of 27 months in 378 patients [16]. These findings imply an additional value of blood NfL measurements for disease monitoring, which may be complementary to brain MRI.

In a monocenter, prospective registry, serum GFAP correlated with verbal fluency, visuomotor and executive functions in patients with CSVD [17]. Lately, in a follow-up study over 12 months, vascular endothelial growth factor (VEGF) levels in the blood were associated with incident brain lesions in a longitudinal study [18]. Beyond that, such biomarkers have demonstrated substantial diagnostic and longitudinal value in other neurological disorders, including multiple sclerosis and neurodegenerative diseases [19, 20].

The present prospective cohort study builds upon a previously conducted single-center pilot study by our group (local Ethics approval no. 343/22), which demonstrated the feasibility of longitudinal biomarker measurements in patients with CSVD and provided preliminary evidence supporting associations between biomarker dynamics and MRI-detected CSVD progression.

The objectives of the presented study include the identification of one blood biomarker or a set of biomarkers that can help identify disease progression in CSVD. A further aim is to describe differences of biomarker courses in direct comparison of patients with CSVD and acute lacunar ischemia with patients with territorial ischemia in a prospective, consecutive and multi-modal trial.

